### Outcomes

The primary endpoint of the study will be the change in HbA1C within the groups and the differences between the groups. HbA1c will be measured at baseline, 3-month, 6-month, 9-month, and 12-month follow-up visits in all participants. The primary time-points for HbA1C are the 6- and 12-month measurements (Table 1).

The secondary outcomes of the study include differences in the mean cholesterol, LDL cholesterol, HDL cholesterol, systolic and diastolic blood pressure, triglycerides, microalbuminuria, waist circumference, body mass index, and muscle mass index. The laboratory measurements will be performed at the beginning of the intervention and at month 12 (Table 1). The anthropometric measurements will be done every 3 months. In addition, secondary outcomes will be treatment compliance measured by the Morisky score [23], quality of life using the Short Form 36 Health Survey Questionnaire (SF-36) [24], nutritional habits assessed by the ENSANUT questionnaire [25], and physical activity by the international physical activity questionnaire [26]. In addition, anxiety and mental health will be evaluated using the Beck questionnaires [27, 28]. The questionnaires will be applied at baseline and at 12 months of the intervention (Table 1).

Finally, process indicators related to the use of mobile application and the information board (usage time and frequency, user satisfaction among others) will also be assessed.

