### Sample size calculations

Considering a difference in HbA1c of 1.0% between the intervention and the control group, a standard deviation of 1.5%, a power of 90%, and an alpha of 0.05 (two-sided tests) with a drop-out rate of 25% during the study, a minimum of 126 will be needed in total in each of the three states. As each state where this study will be carried out has a different healthcare provider, we decided to stratify the analysis according to participating state to see whether the intervention works regardless of the healthcare provider. Thus, 126 participants will be recruited in each state. Thus, the total number of patients will be 378. The reason for testing the intervention in each state differently is as the patients belong to different healthcare providers. There may be differences between these systems. We would like to see whether the intervention works within each of the healthcare provider’s systems.

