#### Primary and secondary endpoint analysis

The primary endpoint of the study will be the change in HbA1c between the intervention and the control group. This will be assessed by a repeated measurement approach based on mixed models which contain both fixed effects and random effects. These models are likelihood-based approaches in the presence of non-ignorable missing data (e.g., missing at random). the main purpose will be to determine whether the within-person changes over time vary across levels of one or more between-person factors (e.g., blood pressure measurement technique and for the same covariates included in the model for coprimary endpoints). Exploratory analysis will consist of profile graphs and Pearson’s correlation matrix. The Mauchly test will be applied to verify the fulfillment of the Huynh-Feldt condition. A mixed linear model will be used. To select the most appropriate covariance matrix, the Alkaike AIC or the Swartz BIC criteria will be used. The models will be controlled for age, sex, and time with the diagnosis of diabetes. No subgroup analysis will be conducted. Also, interim analyses will not be performed in this study.

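### The protocol defines its primary endpoint in conflicting ways: within-arm change and two primary visits in one place, a between-arm change with no visit in another, and a sample size for one comparison

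*Protocol article*

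**What the plan says.** The Outcomes section of the protocol article defines the endpoint in two parts: "The primary endpoint of the study will be the change in HbA1C within the groups and the differences between the groups". The Method paragraph of the Abstract uses the same wording. Outcomes then adds: "The primary time-points for HbA1C are the 6- and 12-month measurements".

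The section on primary and secondary endpoint analysis gives a different definition: "The primary endpoint of the study will be the change in HbA1c between the intervention and the control group". It names no visit. On the method it says: "This will be assessed by a repeated measurement approach based on mixed models which contain both fixed effects and random effects". The stated purpose of the model is to "determine whether the within-person changes over time vary across levels of one or more between-person factors". The example given for such a factor is "blood pressure measurement technique and for the same covariates included in the model for coprimary endpoints".

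The sample size section assumes one difference of 1.0% between intervention and control, an SD of 1.5%, 90% power and "an alpha of 0.05 (two-sided tests) with a drop-out rate of 25% during the study". It does not say to which visit the difference refers. Nothing in the article splits alpha, orders the two visits, or says whether one or both must succeed.

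**The concern.** The text has three versions of what decides the trial. Outcomes and the Abstract include change within each arm. The analysis section has only the comparison of arms. The sample size supports one such comparison, while Outcomes names two primary visits.

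The within-arm part matters most. A fall in HbA1c inside the app arm does not isolate the effect of the app. Patients are eligible because their HbA1c is above 8.5%, and a group selected on a high value tends to be lower when measured again, whatever it receives. Usual care may also lower it. Randomisation makes this fall equal in expectation in the two arms, so it cancels in the between-arm difference but not in either within-arm change.

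The model paragraph should settle which contrast is tested, but its example comes from some other study. This trial compares no blood pressure techniques, and the article defines no coprimary endpoints. Treatment arm by visit is never named as the term of interest. At stake is whether a reader of the results can tell which single number was meant to decide the trial.

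**Working it through.** **1. What the sample size supports.** Inputs from the sample size section: difference 1.0, SD 1.5, two-sided alpha 0.05, power 90%, drop-out 25%. Allocation is 1:1 (Random allocation section).

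- Completers per arm = 2 × [1.5 × (1.960 + 1.282) / 1.0]² = 47.28.
- Total per state = 2 × 47.28 / 0.75 = 126.1, against 126 stated. Rounding up at each step gives 64 per arm, or 128.

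The stated figure is therefore the size for one between-arm test at 0.05. Nothing in it allows for a second primary visit or for a within-arm test.

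**2. The definitions side by side.**

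| Place | Within-arm change primary? | Between-arm difference primary? | Visit |
|---|---|---|---|
| Abstract | yes | yes | not named as primary |
| Outcomes | yes | yes | months 6 and 12 |
| Endpoint analysis | no | yes | none |
| Sample size | no | yes, one | none |

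**3. Two visits.** Suppose that significance at either visit were enough, each tested at two-sided 0.05. With Z₆ and Z₁₂ standard normal under no effect and correlated by ρ, the false-positive rate is 1 − P(|Z₆| ≤ 1.96 and |Z₁₂| ≤ 1.96). The article gives no ρ, so a range is assumed.

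| ρ | Rate |
|---|---|
| 0.5 | 9.1% |
| 0.7 | 8.35% |
| 0.8 | 7.8% |
| 0.9 | 7.0% |

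If both visits must be significant, or if a single arm-by-time test decides, the rate does not exceed 5%.

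**4. What each repair costs in sample size.**

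- One between-arm contrast at one visit: 126 per state, 90.0% power with 126 / 2 × 0.75 = 47.25 completers per arm.
- Either visit sufficient, 0.025 each: 55.85 completers per arm, 2 × 55.85 / 0.75 = 148.9, so 149 per state (150 with equal arms). At 126 per state the power per visit falls to 84.1%.
- Both visits required: no alpha split. If each visit has 90% power, joint power lies between 1 − 0.10 − 0.10 = 80% and 90%.

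**5. Fall expected from selection alone (illustration).** Assume that HbA1c in the source clinics is normal with mean μ and SD σ, that the qualifying value above 8.5 is also the baseline, and that repeat values correlate by r. With a = (8.5 − μ)/σ, the expected fall is (1 − r) × σ × φ(a) / [1 − Φ(a)].

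- μ = 7.5, σ = 1.5, r = 0.7: 0.3 × 1.5 × 1.265 = 0.57 points.
- μ = 8.5, σ = 1.5, r = 0.9: 0.1 × 1.5 × 0.798 = 0.12 points.

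Widening to σ of 1.5 to 2.0 and r of 0.6 to 0.9 gives about 0.1 to 0.9 points. The direction follows from the entry rule. The size does not follow from the document, because μ, σ and r for the clinics are not given.

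**The case against.** The strongest reply is that an endpoint description is not a success rule. No sentence says that a fall within one arm, or a difference at one visit, would count as success. The aim is to compare two strategies, the sample size rests on a between-group difference, and the analysis section names only that comparison. The purpose it gives for the model is close to a group-by-time test. Read generously, the two-part wording in Outcomes is a loose description of that model. Rules on multiplicity may also sit in an analysis plan that is not shown.

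Much of this stands, and it rules out three stronger readings that a reader might infer.

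- *That the protocol lets a within-arm fall, or one visit, be declared a success.* It does not say so. It labels within-arm change primary and leaves the relation between the visits open.
- *That the false-positive rate is 22% to 25%.* This takes the either-visit rate of 7.8% to 9.1% (ρ of 0.8 to 0.5) over three states: 1 − (1 − 0.078)³ is about 22% and 1 − (1 − 0.091)³ about 25%. It needs success in any one state to count. The sample size section wants to know whether the intervention works whoever the provider is, which points to consistency across states.
- *That a within-arm test has a known high chance of being significant.* With 47 completers, SD 1.5 and the μ of 7.5 to 8.5 and r of 0.7 to 0.9 spanned in step 5, that chance runs from about 24% to 95%, which shows how little the document pins down. It also needs the qualifying HbA1c to be the baseline. The screening section suggests this by placing the remaining baseline tests after it, but Table 1 is not shown. A fresh HbA1c at t0 would make the fall smaller.

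What the reply does not remove is the contradiction. The analysis section does not withdraw the within-arm part and chooses neither of the two visits. An unseen analysis plan would not change the conflicting definitions or the misplaced clause in the protocol itself.

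**Conclusion.** The protocol contradicts itself on its primary endpoint, labels as primary a quantity that cannot show an effect of the app, and names two primary visits on a sample size built for one comparison.

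The visit question is moderate in size: about 7% to 9% instead of 5%, and only if either visit were taken as sufficient at an unadjusted 0.05, with an assumed correlation of 0.5 to 0.9. It is nil under a both-visits rule or a single arm-by-time test. The within-arm part is the more serious, because some fall is expected in both arms under this entry criterion. Its size cannot be stated from the document. The between-arm contrast itself is not biased by that fall.

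**What to change.** In the Abstract, Outcomes and the endpoint analysis section, state the same single primary estimate: the between-arm difference in HbA1c change from baseline at one named visit, taken from the arm-by-visit term of the mixed model and tested at two-sided 0.05. Month 12 is a natural choice because it is the end of the intervention. Test the other visit only if the first is significant. Alternatively, keep both visits as primary and state that both must succeed.

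Report within-arm changes descriptively. In the model paragraph, replace "blood pressure measurement technique and for the same covariates included in the model for coprimary endpoints" with a reference to treatment arm by visit.

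This is a change of wording. With one primary visit, month 6 (if month 12 is chosen) loses its co-primary status and the sample size stays at 126 per state. If both visits must succeed, alpha needs no split, but power for the joint claim is at most 90%.

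### The only endpoint analysis described is built for five-visit HbA1c; as worded it reduces to a change-score comparison for the 11 secondary outcomes measured twice and leaves their baseline values unused as covariates

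*Protocol article*

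**What the plan says.** All references are to the Methods of the protocol article.

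- *Outcomes*, measurement times. For the laboratory outcomes: "The laboratory measurements will be performed at the beginning of the intervention and at month 12". For the questionnaires: "The questionnaires will be applied at baseline and at 12 months of the intervention". Anthropometric measures are taken every three months. HbA1c is measured at baseline and at months 3, 6, 9 and 12. The text gives no schedule for blood pressure, and Table 1 is not visible in the copy reviewed.
- *Outcomes*, wording of the first list: "The secondary outcomes of the study include differences in the mean cholesterol", followed by the other laboratory, blood pressure and anthropometric outcomes. The questionnaires come in later sentences without that phrase.
- *Primary and secondary endpoint analysis* gives a single method, a mixed model for repeated measurements. Its aim is stated as: "the main purpose will be to determine whether the within-person changes over time vary across levels of one or more between-person factors". It adds: "The Mauchly test will be applied to verify the fulfillment of the Huynh-Feldt condition". The covariance matrix is chosen by AIC or BIC, and the models are adjusted for age, sex and diabetes duration. The sentences in this section name only HbA1c.
- The section on non-adherence and missing data plans intention-to-treat analysis, with multiple imputation for participants who withdraw.

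**The concern.** A model of trajectories, a sphericity test and a covariance search presuppose several follow-up visits. With one baseline and one month-12 value there is a single within-person difference, so sphericity holds trivially and there is no trajectory to model. What remains is the arm-by-time term. If baseline is a free response, that term is the difference between arms in mean change.

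The strongest predictor usually available for a month-12 value is the same outcome at baseline. It will already have been collected, yet it is not among the listed covariates. At stake is the width of the confidence intervals for lipids, microalbuminuria, adherence, quality of life, diet, physical activity and mood. A smaller matter is that, for the five laboratory outcomes, the mean-difference wording in *Outcomes* and the change wording in the analysis section do not clearly name the same contrast.

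**Working it through.** **The plan's own figure.** The sample size rests on HbA1c: "Considering a difference in HbA1c of 1.0% between the intervention and the control group", "a standard deviation of 1.5" percentage points, 90% power and two-sided alpha 0.05. Per arm, 2 × (1.5 × (1.960 + 1.282))² / 1.0² = 47.28. Both arms with 25% drop-out: 2 × 47.28 / 0.75 = 126.1, which matches the stated 126 per state and 3 × 126 = 378. Nothing below changes this figure.

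**Count of outcomes.** The first list has ten: total, LDL and HDL cholesterol, triglycerides, microalbuminuria, two blood pressures, waist, BMI and muscle mass index. The questionnaires add six, counting each once and Beck as two. Of these 16, five laboratory + six questionnaire = 11 have two time-points in the text. Three (waist, BMI, muscle mass index) are three-monthly. The two blood pressures are unplaced; if they were also measured only twice, the count would be 13.

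**Equivalence.** In one simulated complete dataset (141 per arm, correlation 0.6):

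| Analysis | Estimate | SE |
|---|---|---|
| Mixed model, arm-by-time, free baseline means | -0.1425 | 0.0959 |
| Change-score comparison | -0.1425 | 0.0959 |
| Month-12 value adjusted for baseline (ANCOVA) | -0.156 | 0.0880 |
| Mixed model, baseline means constrained equal | -0.156 | 0.0867 |

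In a second simulated dataset (126 patients, correlation 0.5), adding age as a main effect left the arm-by-time SE at 0.1609. Adjusting for the outcome's own baseline gave 0.145.

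**Variance ratio.** The documents give no baseline to month-12 correlation r, so it is assumed. With equal SDs, the variance is proportional to 2(1-r) for the change score and to 1-r² for ANCOVA, so the complete-data ratio is 2/(1+r). If a fraction 0.25 lacks month 12 at random, a likelihood fit with free baseline means also uses the drop-outs' baselines, and the ratio becomes 1 + 0.75(1-r)/(1+r).

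| r (assumed) | Ratio, complete data | Interval wider by | Ratio, 25% drop-out | Interval wider by |
|---|---|---|---|---|
| 0.3 | 1.54 | 24% | 1.40 | 18% |
| 0.5 | 1.33 | 15% | 1.25 | 12% |
| 0.7 | 1.18 | 8% | 1.13 | 6% |
| 0.9 | 1.05 | 3% | 1.04 | 2% |

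The widening is the square root of the ratio. Simulation of complete trials gave 1.56, 1.34 and 1.17 at r = 0.3, 0.5 and 0.7. Simulation with 63 per arm and 25% drop-out gave 1.25 at r = 0.5.

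**Month-12 means alone.** The ratio to ANCOVA is 1/(1-r²): 1.10, 1.33 and 1.96 at r = 0.3, 0.5 and 0.7. The change score beats this comparison only when r exceeds 0.5. ANCOVA is at least as precise as either.

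**Power, illustration only.** Assume an effect of 0.3 SD and 378 × 0.75 / 2, about 141 evaluable per arm, with the complete-data formulas. Change score against ANCOVA is 57% v 75% at r = 0.3, 71% v 83% at 0.5, and 90% v 94% at 0.7. The Abstract and *Trial design* give 1440 patients instead. Then 1440 × 0.75 / 2 = 540 per arm, and at r = 0.5 both analyses exceed 99%.

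**The case against.** The case on the other side has four parts.

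1. **Scope.** No sentence in the analysis section applies the mixed model to a secondary outcome; only the heading does. A condensed article may leave secondary methods to a plan that is not shown. This stands as a limit on how firmly the point can be put. It does not remove it: the article prints one method under a heading that covers both kinds of endpoint, and that method does not fit most of the secondary outcomes.

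2. **The collapse is conditional.** A reader might infer that the model must become a change-score test. The article does not support that. It does not say whether baseline is a free response, a constrained response or a covariate, and either of the last two recovers the precision. With drop-out, a likelihood fit is also no longer exactly a change score. Under the planned multiple imputation, each completed dataset again yields the change-score contrast. Provided baseline is in the imputation model, however, the pooled precision should lie near the drop-out column above rather than the complete-data one.

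3. **Validity.** A reader might infer biased or invalid tests. Under randomisation the change-score contrast is unbiased and its type I error is correct. An empty Mauchly test does no harm, and no power is claimed for any secondary outcome.

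4. **Two contrasts.** A reader might infer conflicting definitions for all 11 outcomes. The mean-difference phrase governs only the first list, so it does not reach the six questionnaires. For the five laboratory outcomes it is loose rather than contradictory, because a model-based difference would satisfy it.

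**Conclusion.** The point holds as a free gain in precision. The one analysis described is written for HbA1c and, as worded, does not suit 11 of the 16 secondary outcomes. If baseline is an unconstrained response, variance exceeds that of a baseline-adjusted analysis by 5% to 54% in complete data over r = 0.9 to 0.3. In a likelihood fit with 25% random drop-out the excess is about 4% to 40%.

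The size rests on r, which is assumed, on equal SDs at the two visits, and on the unstated role of baseline. A power loss such as 71% against 83% should not be read as a property of this trial: it also needs an assumed 0.3 SD effect, complete-data variances and 378 patients, whereas the article gives both 378 and 1440. The primary analysis and the sample-size calculation are unaffected.

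**What to change.** State in *Primary and secondary endpoint analysis* that:

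- the repeated-measures mixed model, with its covariance selection, applies to HbA1c and to outcomes with three or more visits;
- each outcome measured only at baseline and month 12 is compared between arms at month 12, adjusted for its own baseline value and for age, sex and diabetes duration, or equivalently by a mixed model with baseline means constrained equal across arms;
- this is done within the planned intention-to-treat and multiple-imputation approach, so that participants without a month-12 value are not simply dropped;
- the adjusted mean difference is reported with a 95% confidence interval, and the Mauchly test and covariance search are omitted for these outcomes.

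Assign blood pressure to one group or the other according to its schedule in Table 1. In *Outcomes*, make the mean-difference wording refer to this adjusted month-12 contrast.

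The cost is a few sentences of analysis text, with no new data, visits or patients.

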### Data analysis plan

All data collected locally at each enrolling unit will be recorded into an electronic database. Clinical data to be input into the database include demographic information, results on blood and urine laboratory tests performed in each center, ongoing treatment (dose and medication), as well as information on adverse events during follow-up of the trial. The quality of data obtained will be validated by expert personnel at each study site.

#### Data management

All data will be entered twice (double data entry) and checked by two independent administrators to improve the quality and accuracy of data. The data obtained in this study will be stored at the Consejo de Salubridad General of Mexico in an electronic database. Only the data administrators and statistician will have access to the stored data. They will also be responsible for data backup. All data will be archived at the Consejo de Salubridad General of Mexico for a minimum of 5 years from the study end.

#### Confidentiality

The information collected will be used for research purposes and be analyzed without the personal identification of the participants. None of the personal information of enrolled participants will be shared or released.

#### Descriptive analysis

The first step in the data analysis will be a descriptive analysis that will summarize continuous variables using mean value, median, standard deviation, and interquartile range. Categorical data will be described using absolute and relative percentages. The incidence of adverse events will be tabulated by the treatment group.

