**Exclusion criteria**	
- Pregnancy, within 3 months post-partum or planning pregnancy during the trial - Breastfeeding - Serious medical condition (i.e., dialysis) - Not be a permanent resident of the participating states	

Participants who are pregnant, within 3 months postpartum or planning pregnancy during the trial; are breastfeeding; have a serious medical condition that, in the opinion of the investigator, makes them ineligible (i.e., dialysis treatment); have been admitted to hospital within the last 3 months for hyperglycemia or hypoglycemia; or are not permanent residents of the states the study is conducted are not eligible to participate in the study.

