### Interventions

Participants assigned to the intervention group will use a mobile application on their smart phones that will assist them with their diabetes control, provide and update information on their clinical history, offer a monitoring of their nutritional and physical activity habits as well as anthropometric measurements, provide recommendations how to improve on nutritional habits and physical activity behavior, and assist in planning and reminding on clinical appointments. The mobile health application was tested and evaluated in a pilot project in 31 DM2 patients as part of this project. Based on the feedback received, the mobile application was revised and finalized to be sued in this project.

The content and description of the patient mobile health application are presented in Table 3.

**Table 3 Tab3:** Description of the patients’ mobile health application.

Subject	Description of content
Patient profile	Patient’s personal information, as well as information regarding clinical history, laboratory measurements, and current pharmaceutical treatment.
My state of health	Information about age, body weight, height, body mass index, glucose, total cholesterol, triglycerides, blood pressure, and glycated hemoglobin (HbA1c).
My measurements	Information about serum glucose, blood pressure, heart rate, respiration frequency, and oxygen saturation.
My studies	Information is classified into three analysis sections. A) Health center laboratory; Serum glucose, total cholesterol, triglycerides, glycated hemoglobin (HbA1c), creatinine and urea. B) Alternate laboratory (Lab Salud Digna); Serum glucose, total cholesterol, HDL cholesterol, LDL cholesterol, triglycerides, HbA1c, serum creatinine, serum albumin and urea. C) Complementary studies: information about of ECG, check-ups to assess diabetes complications (retinopathy, nephropathy, neuropathy) study visits.
My medications	Record of pharmacological treatment with its doses.
My body	interactive module monitoring nutritional habits, physical activity, patients’ self-perceived mood, and taking care of my feet. This module also contains a section that allows the patient to view changes and trends in their anthropometric measurements.
My recommendations	Provides recommendations on healthy eating habits, physical activity, mental health, and taking care of my feet.
Medical appointment	Information on upcoming clinical appointments (clinical control, laboratory tests).

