Contact	Interactive module allowing patients to provide questions and comments about the mobile application.

The participating physicians will have access to the patient’s information through a mobile information tablet. That specific tool will allow the physician to view and consult all patient information of the patient’s mobile application. It will use a Java programming language, having an exchange of information through the Apache Web Server and from the Tomcat Application Server in a Java environment inbuilt on the SQL Server manager. Thus, the participating physician will have direct access to all clinical information, visits, lifestyle changes, and cardio-metabolic control of the DM2 patient. The main idea is that the mobile information board will help the physician to monitor better the treatment and control of his patients.

Participants assigned to the control arm will continue their diabetes care without mobile health technology assistance. This comparer was chosen as it is the current standard of care in the Mexican primary healthcare system.

The duration of the intervention will be 12 months. Each patient will be invited to follow-up visits and measurements every 3 months (month 3, month 6, month 9, and month 12).

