### Ethical considerations

The study protocol was approved by the Ethical Committee in Research, Secretaria de Salud, State of Colima-Mexico approved this study: 2021/1/CR/BS/EPI/162. Each study participant will sign informed consent. Study participants can withdraw from the trial at any time. Participants can also choose to pause or stop receipt of text messages or e-mails by written notice or contacting the trial office by phone. Information on adverse events will be registered on a regular basis. The occurrence of serious unexpected adverse events related to the intervention will be determined by the principal investigator and reported according to local procedures. The trial will be conducted according to the principles of the Declaration of Helsinki and in accordance with other relevant national guidelines, regulations, and acts and using Good Clinical Practice guidelines. Lilly Global herald partnership program is sponsoring the trial. Finally, this is an investigator-generated study and will be performed in full independence of the study sponsor from any other funding body.

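### Adverse events are tabulated by arm with no stated rule that they be found the same way in both arms, although only the intervention arm's physicians see app data

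*Protocol article*

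**What the plan says.** Under Descriptive analysis, the protocol article states: "The incidence of adverse events will be tabulated by the treatment group". No test is attached, and no other safety analysis is given. On collection, the Data analysis plan section has adverse events entered at the enrolling units with the other clinical data, and Ethical considerations adds: "Information on adverse events will be registered on a regular basis".

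Under Interventions the arms differ: "Participants assigned to the intervention group will use a mobile application on their smart phones that will assist them with their diabetes control". The measurements module in Table 3 holds "Information about serum glucose, blood pressure, heart rate, respiration frequency, and oxygen saturation". Of the physician's tablet the article says: "That specific tool will allow the physician to view and consult all patient information of the patient’s mobile application". Its purpose is that "the mobile information board will help the physician to monitor better the treatment and control of his patients". Controls carry on with usual care and no app. The Discussion says that the project's tools include prompts for glucose checks and a glucometer link.

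Under Blinding, patients and physicians know the allocation. Blinding is stated for the HbA1c laboratory staff and the statistician only. Both arms are invited to the same visits at months 3, 6, 9 and 12. Under Monitoring, the Data Monitoring Committee periodically reviews compiled adverse event data and can recommend that the trial be suspended or stopped early.

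**The concern.** A by-arm incidence table reads as a comparison of risk only if an event has the same chance of being recorded in either arm. Here the intervention is partly a monitoring system. It prompts glucose checks and puts more patient data in front of a physician who knows the allocation. Nothing stated keeps that extra information out of the adverse event counts or separates events that came to light through it.

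If it does prompt recording, the intervention arm gathers events that would go unrecorded in controls. The app could then look harmful when it is not, or a real reduction in events could disappear. The table matters beyond description, because the Data Monitoring Committee acts on adverse event data and a reported serious adverse event is a listed ground for withdrawal. Glucose-related events seem the most exposed. That is an inference from what the app does; the article does not say it.

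**Working it through.** The plan gives no adverse event rate, detection rate or expected count, so there is no figure of its own to reproduce. The check has two parts.

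**1. Sources of event information, by arm**

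| Source | Intervention | Control |
|---|---|---|
| Visits at months 3, 6, 9, 12 | yes | yes |
| Coordinator contact with participants | yes | yes |
| Electronic Health Record at the centers | yes | yes |
| App with glucose prompts and glucometer link | yes | no |
| Physician's view of app data | yes | no |

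The first three sources are common and the last two are not. The article does not say which of them feed the adverse event record.

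**2. Size, if the unshared sources do feed it**

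Observed incidence = true incidence × probability of detection. Hence observed risk ratio = true risk ratio × (detection in intervention ÷ detection in control).

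Inputs:
- True 12-month incidence: 20% in both arms (assumption).
- Detection: 80% with the app, 60% or 50% without (assumption).
- Patients per arm: the article gives two totals, 378 under Sample size calculations and 1440 under Trial design. With 1:1 allocation these are 189 and 720 per arm.

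Results with a true risk ratio of 1:
- 80% v 60%: observed 16% v 12%, ratio 0.80/0.60 = 1.33. Expected counts are 189 × 0.16 = 30.2 v 189 × 0.12 = 22.7, or 115.2 v 86.4 at 720 per arm.
- 80% v 50%: observed 16% v 10%, ratio 0.80/0.50 = 1.6. Expected counts are 30.2 v 18.9, or 115.2 v 72.0 at 720 per arm.

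The 20% affects the counts but cancels from the ratio. A wider assumed range, 90% in the intervention arm v 75%, 60% or 45% in control, gives ratios of 1.2, 1.5 and 2.0.

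Masking: a true reduction is shown as no difference when the true ratio is the inverse of the detection ratio, that is 1/1.33 = 0.75 or 1/1.6 = 0.625.

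Effect of the shared visits: let v be the share of events found through the common sources in either arm, and a the share of the remainder found only through the app or board. The detection ratio is [v + a(1 − v)]/v = 1 + a(1 − v)/v. With v = 0.60 and a = 0.5 this is 0.80/0.60 = 1.33. With v = 0.50 and a = 0.6 it is 0.80/0.50 = 1.6. As v approaches 1, or a approaches 0, the ratio approaches 1. Complete, identical questioning at the shared visits is therefore what shrinks the bias.

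**The case against.** The strongest reply is that tabulating adverse events by arm is standard, no between-arm test is stated, and the wording of event questions and source flags is usually left to the full protocol or case report form. The schedule of assessments (Table 1) is not visible here, so a common adverse event assessment may exist. This is a fair limit on confidence. It does not remove the point, which concerns a stated by-arm table set beside a stated difference in monitoring. A descriptive table by arm still invites a comparison.

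The second reply is that the route from app to adverse event record is not documented. That is correct. The article gives no source for registered events, and the Table 3 readings could be clinic values carried over from the health record. The detection ratio could be 1.0. The figures above restate assumed detection rates and do not estimate the bias.

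Three stronger readings are tempting and not supported:
- *That the table could hide a harm.* Higher detection in the intervention arm works the other way: a true ratio of 1.5 with a detection ratio of 1.5 would appear as 1.5 × 1.5 = 2.25. Hiding a harm needs lower detection in that arm, which nothing in the article shows. A reader might dismiss a real excess as extra monitoring, but that would be an error of interpretation.
- *That the protocol names glycaemic events as adverse events.* It mentions them only as a reason for exclusion, for patients who "have been admitted to hospital within the last 3 months for hyperglycemia or hypoglycemia". Admissions are also among the events least dependent on an app.
- *That control physicians learn of events only at visits.* Coordinator contact and the electronic record are available for both arms.

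**Conclusion.** The point holds in a conditional form. The arms differ by design in how much event-revealing information reaches an unblinded physician, and no stated rule makes the by-arm counts rest on events found the same way. If that information prompts recording, the table mixes detection with risk and errs towards a false excess in the intervention arm or a masked reduction.

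The size is unknown. A false ratio of 1.33 to 1.6 follows from assumed detection of 80% v 60% to 50% and equal true risk; the shared 3-monthly visits reduce it. No sample size, HbA1c analysis or clinical rule is affected. The change is worth making because an event's source is hard to reconstruct once the trial is over.

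**What to change.** Under Descriptive analysis, define the comparative by-arm table as events elicited by one identical scripted question in both arms at the existing month 3, 6, 9 and 12 visits. Name hypoglycaemia and hospital admission for hypo- or hyperglycaemia as items. Add admissions from the Electronic Health Record if it captures them at all sites; the article does not confirm this, so it must be checked first.

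Count every event reported at a visit, even if the app or board detected it first. Dropping such events would remove intervention-arm events that patients would have reported anyway while keeping the same events in controls, which reverses the bias. Flag the source of each event and show a second by-arm table of all events from any source, so that no safety information is lost.

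The cost is one scripted question and a source flag on the adverse event form, plus a second table. App users may still recall events better because they have been tracking their readings. The report should state this as a residual limitation.
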